#### 2.8.4. Additional Analyses

Analysis of demographics and baseline characteristics will be descriptive with appropriate summary statistics calculated. Subgroup analyses for the primary endpoints for sensitivity analyses will be conducted. All primary analyses will follow the intent-to-treat principle. The maximum likelihood estimation method will be used to deal with any missing data, assuming that data are missing at random. Sensitivity analyses will be carried out with various assumptions of missing mechanisms. Unblinded CGM offers the prospect of direct benefit with the potential to reduce hyper- and hypoglycemia in the concerned population and has been shown to be safe and effective in children, and we want to collect data for other variables such as DKA and serious hypoglycemia even if the unblinded CGM has no efficacy on TIR; thus, no interim analysis is planned.

### 2.9. Study Administration

The UMN Coordinating Center is led by [name], who has overall responsibility for the study. The Coordinating Center is responsible for maintaining quality assurance and quality control systems to ensure that the trial is conducted and data generated, documented, and reported in compliance with the protocol, Good Clinical Practice and applicable regulatory requirements. [name], the Ugandan PI, has responsibility for all study activities in that country. [name] and [name] [name] from the Ugandan Ministry of Health (MOH) is performing the cost analyses and is responsible for presenting these findings to the MOH to assist in policy determination. A DSMB with two members from East Africa and one from the US met by conference call every 6 months. As this is a low-risk study, there is no external monitor, but the internal monitoring is done by the DSMB. Any protocol modifications are reported to both the local and Minnesota Research Ethic Committees. All records at UMN and in Uganda are kept in a secure location and will be kept for as long a period as dictated by local IRB and Institutional regulations.

If any serious unanticipated adverse device effect (UADE) occurs, the use of the study device may be suspended or stopped completely, pending DSMB review. Also, study activities could be suspended if the manufacturer of any constituent study agent requires stoppage of agent use for safety reasons (e.g., product recall). If any death occurs in the study and is assessed to be related to the study treatment device by the study site investigator, enrollment in the trial will be halted, pending DSMB review. A manuscript is to be published to share our work with the broader diabetes community globally.

## 3. Results and Progress

In August 2022, the Uganda study team was trained for five weeks on the protocol, CGM use, interpretation of CGM and SMBG data, and research principles by the Minnesota study team. Video calls every 2–4 weeks and in-person visits by the Minnesota team twice per year provide ongoing monitoring and mentorship. Recruitment began in August 2022. Two of the planned four cohorts have completed the study and the third cohort is in progress. As of August 2025, 136 participants had been enrolled, ~75.0% of the target sample size of 180 in Figure S1 [19]. We hope to complete the enrolment of participants by 31 March 2026 and complete the last patient follow up by 30 April 2027. The study will be completed in August 2027 with a manuscript preparation.

## 4. Discussion

This protocol describes the background, design, and organization of a randomized clinical trial to determine whether CGM wear improves glucose time-in-range (which could include reducing time in both hyper- and hypoglycemia) in children and youths with type 1 diabetes in Uganda. Importantly, it involves a cost-effectiveness analysis since the economics of CGM use in this region may be quite different from what has been found in the high-income countries where it has become standard-of-care. The study involves a large number and wide age range of children and young adults from a low-resource country, making the results potentially generalizable for wider applicability in sub-Saharan Africa. Involvement of the local Ministry of Health economists allows assessment of the real-world practicality of this intervention in improving diabetes care in a low-resource setting.

CGM has rapidly become standard-of-care in the US and Europe but is virtually unknown in resource-poor settings. A decade ago the most frequent cause of TID-related death in Africa was reported to be lack of insulin [20]. While insulin and diabetes test strips are still far from universally available worldwide, this is no longer the case for most children in Uganda and in much of the world where CDiC and Life for a Child have stepped in to provide basic diabetes therapies. When children were dying because insulin and test strips were not at all available, the goal was to provide a somewhat arbitrarily determined “minimal level of acceptable care”, which was primarily intended to keep them alive. However, marked improvements in insulin and test strip availability now challenge the assumption of what constitutes “acceptable care”, and raise questions about the quality of care. This is because diabetes metabolic control is still poor in these children, and they are regularly experiencing catastrophically high and low blood glucose levels [21,22,23,24,25].

All patients in this study, including those in the control group, will receive more intensive education, greater attention from the diabetes team, and more test strips than are commonly available today. If this approach results in similar levels of improvement in glucose TIR in control subjects using SMBG compared to patients who use unblinded CGM, this study will have performed an important service by demonstrating that there is no need for this expensive therapy and that, instead, more focus needs to be placed on patient education and interaction with the medical team. But if CGM leads to significantly greater improvement in diabetes metabolic control by reducing hyper- and hypoglycemia, then the ethical question is not whether to provide this therapy in resource poor settings but how to make it affordable. This is similar to the issue that arose when HIV/AIDS therapies first became available. Such decisions must be guided by data obtained in the specific and unique settings found in low, low-/middle income nations. The goal of this protocol is to obtain these data.

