### 2.3. Overview, Study Design

This randomized, non-blinded, phase 4 clinical trial is programmed as follows. Subjects are assigned 1:1 to the CGM Group or the Control Group. Randomization is stratified by clinic and by age group (4–11, 12–18, and 19–26 years) with approximately equal numbers in each age group and of the two clinic locations. The random numbers were generated by the statistician using a central computer. At baseline, a 1–2 weeks initial assessment is performed where the ability to wear and return the sensor can be demonstrated, as an entry criterion for randomization. After this, 180 children and young adults with T1D will be randomized into the clinical trial in four 12-month cohorts of 45 patients each.

The study design is shown in Figure 1. Half of the subjects (*n* = 90, CGM Group) receive unblinded FreeStyle Libre 2 CGM for the entire 12 months. Half (*n* = 90, Control Group) are given sufficient test strips for three times daily SMBG months 1–6, while wearing blinded CGM for endpoint assessment. For months 7–12 they switch to unblinded CGM. The treatment group is expected to continuously modify their insulin dose and behaviors based on real-time, continuous availability of glucose data. The control group has no access to these data and will base their actions on SMBG measurement alone. For study data analysis, we will use unblinded sensor data from the treatment group and blinded sensor data from the control group that is obtained in the two weeks preceding each monthly visit; thus, the CGM data comparison period will be the same for both groups.

The investigators and the patients are not blinded to treatment arm as there is no practical way to do this. But they are blinded to the comparison data for CGM versus SMBG use until the study is completed. Table 1 lists the schedule of study assessments.

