### 2.7. Sample Size Determination

The sample size is determined based on hypothesis testing of the primary efficacy endpoint. The null hypothesis is that the two arms will demonstrate no significant differences in the six-month change in glucose TIR. The alternative hypothesis is that wearing unblinded CGM will have greater improvement in glucose TIR over six months compared to the control arm. We estimate a standard deviation of 16.6% for baseline TIR based on our pilot data [3] and assume a moderate correlation of 0.5 between baseline and 6-month TIR values. A sample size of 144 patients (72 per arm) will have over 90% power to detect a difference of 8.6% in 6-month TIR changes between the two arms at the one-sided significance level of 0.05. To allow a 20% dropout rate, a total of 180 patients will be randomized with planned study completion of at least 144 patients. The sample size will have over 90% power to detect a 5-percentage point difference in the 6-month change from baseline in percent time < 70 mg/dL (3.9 mmol/L) or a 3.5 percentage point difference in percent time < 54 mg/dL (3.0 mmol/L) at the one-sided significance level of 0.05.

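### The Discussion would read similar TIR improvement as demonstrating no need for CGM, but the trial plans only a superiority test and sets no margin for similarity

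*Protocol article*

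**What the plan says.** Section 2.7 of the protocol article sets a null hypothesis of no difference between arms in six-month TIR change, and a directional alternative that unblinded CGM is better. The trial is sized to have "over 90% power to detect a difference of 8.6% in 6-month TIR changes between the two arms at the one-sided significance level of 0.05". The inputs are stated: "We estimate a standard deviation of 16.6% for baseline TIR based on our pilot data", and the authors "assume a moderate correlation of 0.5 between baseline and 6-month TIR values". No equivalence or non-inferiority margin appears in section 2.7 or in the statistical methods (section 2.8).

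Section 4 (Discussion) then gives two possible outcomes. If the SMBG arm improves to a similar degree, "this study will have performed an important service by demonstrating that there is no need for this expensive therapy", and effort should go instead into education and contact with the medical team. If CGM gives significantly greater improvement, the question becomes how to make it affordable. *Similar* has no numerical definition and no confidence-interval criterion.

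**The concern.** A superiority test asks whether the data are incompatible with no benefit. Failing it does not show that benefit is absent or too small to matter. Because the Discussion sets *similar* against *significantly greater*, and superiority is the only comparison planned, the natural way to apply it is to treat any non-significant result as similar. The article would then claim a demonstration that its design has no rule to deliver.

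The stakes are practical. Under section 2.9, Ministry of Health staff perform the cost analyses and present them to assist policy. An inconclusive TIR result reported as showing no need could count against access to CGM while the data remained compatible with a useful benefit.

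**Working it through.** **Inputs.** From section 2.7: baseline SD 16.6 points, correlation 0.5, 72 completers per arm, difference 8.6 points, one-sided 0.05, 20% dropout. From section 2.3: 1:1 allocation. Assumption: the SD is the same at baseline and six months.

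**1. The plan's own figure.**
- SD of change = 16.6 × √(2 × (1 − 0.5)) = 16.6.
- SE of the difference = 16.6 × √(2/72) = 2.77.
- Power for 8.6 points at one-sided 0.05 = 92.8% (normal) or 92.6% (noncentral t). The stated power of over 90% reproduces.
- 144 / 0.8 = 180. The number randomised reproduces.

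**2. Precision.**
- Change scores: 95% half-width = 1.977 × 2.77 = 5.47.
- Baseline-adjusted: SD = 16.6 × √(1 − 0.5²) = 14.38, SE = 14.38 × √(2/72) = 2.40, half-width = 1.977 × 2.40 = 4.74.

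**3. What a non-significant result leaves open.**
- Change scores: the one-sided cut-off is 1.656 × 2.77 = 4.58. An observed 4 points is non-significant, with interval 4 ± 5.47 = −1.5 to 9.5. Any observed difference from 8.6 − 5.47 = 3.13 up to 4.58 is non-significant and still includes 8.6.
- Baseline-adjusted: the cut-off is 1.656 × 2.40 = 3.97, so an observed 4 would just reach significance. Only a narrow band, from 8.6 − 4.74 = 3.86 up to 3.97, is non-significant and includes 8.6. Smaller benefits stay open: an observed 3 gives 3 ± 4.74 = −1.7 to 7.7.

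**4. Chance of a non-significant result when CGM works** (one-sided 0.05, change scores): 7% if the true benefit is 8.6 points, 44% if 5, 58% if 4. The documents name only 8.6 as a between-arm difference; 5 and 4 are illustrative.

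**5. Which margin could support a no-need conclusion.**
- A margin of 8.6 is too lenient. On change scores an observed benefit of 3 points has interval −2.5 to 8.5 and would qualify, although a 5-point benefit lies well inside it.
- For an illustrative margin of 5 and a true difference of 0, two one-sided 5% tests (equivalence in both directions) succeed with probability 2Φ(5/2.77 − 1.645) − 1 ≈ 13% on change scores.
- The rule proposed below uses only the upper 95% limit and is less demanding. It succeeds if the observed difference is below 5 − 5.47 = −0.47, with probability Φ(−0.47/2.77) ≈ 43%. Baseline-adjusted, this is Φ((5 − 4.74)/2.40) ≈ 54%.

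**The case against.** The strongest reply is that the Discussion never says a failed test is the criterion. Its condition is similar improvement, the sentence is Discussion prose, and section 2.8 contains no such decision rule. That is right as far as it goes: reading *similar* as *not significant* is an inference from the contrast the authors draw. But with no other definition offered, the claim of demonstration still has no support in the design.

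A second reply is that at the design difference of 8.6 points a false negative is unlikely (7%), and that baseline adjustment nearly removes the overlap with 8.6. This stands, and it limits the size of the concern for 8.6 itself. It does not help for smaller benefits, and nothing in the document says that a benefit below 8.6 is worthless.

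Three stronger readings are tempting, but the documents do not support them.
- **The power statement is wrong, or holds only one-sided.** The level is declared ("at the one-sided significance level of 0.05") and the figure is correct at that level. Two-sided power is 87% on unadjusted change scores, but about 95% with baseline adjustment. Section 2.8.1 plans a mixed model in which everyone wears a blinded sensor at baseline, so a common baseline mean is available to it.
- **The one-sided 5% level is an error.** It is an openly stated design choice. One may prefer a two-sided test, but nothing is misstated.
- **An increase in hypoglycaemia would go untested.** This rests on a power sentence alone. Section 2.2 sets a non-directional objective for time in the hypoglycaemic ranges, and Table 1 collects severe hypoglycaemia history and adverse events at every visit.

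**Conclusion.** The concern holds for the Discussion sentence. A superiority trial without a margin cannot demonstrate that there is no need for CGM merely by finding no significant difference. With a 95% half-width of about 5.5 points on change scores (4.7 adjusted), a non-significant result can be compatible with benefits of several points, and on change scores with the full 8.6. These figures rest on the protocol's SD of 16.6, correlation of 0.5, equal SDs at both times and 72 completers per arm.

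The sample size and the planned superiority test are unaffected. The problem lies in how a null result would be interpreted, and it can be corrected before the comparative data are seen.

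**What to change.** Report the between-arm TIR difference with a two-sided 95% confidence interval. Reword the Discussion so that a non-significant result is called inconclusive about need unless the upper limit lies below a stated smallest worthwhile benefit. That value should be justified on clinical and economic grounds, be smaller than the 8.6-point design difference, and be fixed before unblinding. If no such value can be agreed, drop the word *demonstrating* and state only which benefits the interval excludes.

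Optionally, add to section 2.7 that power at two-sided 0.05 is 87% on change scores and about 95% with baseline adjustment.

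**Cost.** Wording and one agreed margin; no extra patients. Although 136 of 180 had been enrolled by August 2025, section 2.3 says investigators are blinded to the comparison until completion and section 2.8.4 plans no interim analysis, so a margin set now is still credible. The drawback is that a null trial may often be inconclusive. If the true difference is 0 and the margin is an illustrative 5 points, full equivalence would be shown about 13% of the time and the upper-limit rule met about 43% of the time on change scores (about 54% with baseline adjustment).

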## Figures and Tables

**Figure 1 mps-09-00043-f001:**
[figure not shown]
Study flow diagram figure legend. Dark green color is librepro wear for 2wks, yellow is unblinded CGM wear, blue is for Blinded CGM wear.

**Table 1 mps-09-00043-t001:** Overview of patient schedule activities.

Time (−1 Week, then Monthly)	−1 wk	0	1	2	3	4	5	6	7	8	9	10	11	12
Visit Number	1	2	3	4	5	6	7	8	9	10	11	12	13	14
**Informed Consent/Assent**	X													
**Initial Eligibility Screening, including wearing a single blinded Libre Pro CGM for at least 7 days**	X													
**Final Eligibility, Randomization**		X												
**Complete Medical History**	X													
**Interim Medical History**		X	X	X	X	X	X	X	X	X	X	X	X	X
**Complete Physical Exam**	X													
**Limited/Directed Physical Exam ***		X	X	X	X	X	X	X	X	X	X	X	X	X
**Physical Activity History**		X	X	X	X	X	X	X	X	X	X	X	X	X
**Pregnancy inquiry (as appropriate)**	X	X	X	X	X	X	X	X	X	X	X	X	X	X
**Prior/Concomitant Meds**	X	X	X	X	X	X	X	X	X	X	X	X	X	X
**Adverse Event Assessments**	X	X	X	X	X	X	X	X	X	X	X	X	X	X
**Daily Insulin U/kg/day, Type of Insulin**	X	X	X	X	X	X	X	X	X	X	X	X	X	X
**Severe Hypoglycemia History**	X	X	X	X	X	X	X	X	X	X	X	X	X	X
**Clinic POC HbA1c**	X				X			X			X			X
**Control Group Months 0–6: Libre Pro (blinded) CGM placed in clinic and returned to clinic the following month, test strips dispensed in clinic and SMBG downloaded monthly ****		X	X	X	X	X	X							
**CGM Group Months 0–12 and Control Group Months 7–12: Libre 2 (unblinded) CGMs dispensed in clinic monthly, worn continuously, and completed CGMs returned monthly to clinic**		X	X	X	X	X	X	X	X	X	X	X	X	
**Insulin Dispensed**		X	X	X	X	X	X	X	X	X	X	X	X	X
**Validated Questionnaires *****	X							X						X
**Patient Education**	X	X	X	X	X	X	X	X	X	X	X	X	X	X

* monthly physical exam, ** done monthly for 6 months, *** Questionnaire filled every 6 months.

## Data Availability

Data from this trial will be made available at completion of the study, upon reasonable request to the authors.

## Abbreviations

CGM	Continuous glucose monitoring
HbA1c	Hemoglobin A1c
IDF	International Diabetes Federation
POC	Point of care
RCT	Randomized, controlled trial
SMBG	Self-monitoring of blood glucose (meter, test strips)
T1D	Type 1 diabetes
TIR	Time-in-range, glucose 70–180 mg/dL (3.9–10.0 mmol/L)
UADE	Unanticipated Adverse Device Effect

## Appendix A

**Table A1 mps-09-00043-t0A1:** Protocol development: challenges identified and the approaches to resolving them.

Challenges Recognized During Protocol Planning	Planned Approach
When determining overall study goals and plans, ensuring local significance and impact requires a “ground up” rather than a “top down” approach. Local community support is important.	[name] has been visiting Uganda at least annually since 2007, as part of a clinical collaboration between Mulago Hospital and the University of Minnesota. The strong personal ties that have developed over the years between her and Mulago pediatric endocrinologist [name] helped foster collaboration in the development of this protocol and the NIH grant. The project originated from concerns raised by [name] about her patients and their needs. She and [name] worked together on all aspects of this protocol. They sought input from their colleagues and from a local diabetes patient and family association (the Sugar Cubes) during the planning. [name] primary role was to organize the project goals into standard research protocol and grant application formats.
Identifying participating sites for a multicenter study should consider subject availability, the experience of the site investigators, and the potential for productive investigator collaboration.	Mulago Hospital, where [name] practices, does not have sufficient patients to complete the entire study. She chose to collaborate with Drs. [name] and [name] at St. Francis Hospital, Nsambya, located about 5 km from Mulago. Mulago and Nsambya are the two largest pediatric diabetes clinics in the country. Drs. [name], [name], [name] and [name] have all previously worked successfully together.
Initial discussions focused on determining the best and most doable intervention to improve diabetes metabolic control.	In order to move closer towards diabetes advancements that are standard for patients in well-resourced countries, we considered CGM technology, analog insulin use, or a combination of the two in a 2 × 2 study design. It was decided that doing both was too much of a clinical change all at once for the local teams and patients, and too complex a research protocol for a team that had no experience with RCTs. Of the two, the Ugandan team felt that CGM was the more important first step.
No previous CGM study had been done under these conditions, so there were no relevant data available for power analysis.	To address this, we performed a pilot and feasibility study with a single blinded sensor wear in 78 East African youths with TID to determine patient level of interest, and to assess potential problems in this humid, equatorial environment (e.g., equipment malfunction, difficulty with site adhesion, skin irritation or infection) [3]. The pilot study provided critical data for sample size calculation.
Global research generally requires at least some degree of local institutional experience in grant submission and grant management.	Global Health Uganda, a grants management organization, has extensive experience and also has a longstanding formal relationship managing grants with the University of Minnesota (UMN). Thus, this was a logical partnership. We originally tried to add a site in another East African country, but despite the best efforts of their team and ours, they did not have sufficient research administrative support to proceed.
Global research involves addressing a myriad of local logistical and regular requirements and getting appropriate approvals.	Prior to grant submission, [name] and Research Manager [name] spent time in Uganda with [name] obtaining input and permission from the Ministry of Health and the Ugandan Drug Development Authority. They partnered with Ministry of Health economists in developing the cost-effectiveness component of the protocol. Importing the CGM systems into the country was also a concern. Changing Diabetes in Children (CDiC, Novo Nordisk) provides free insulin, test strips, and HbA1c point-of-care machines for Ugandan youths with diabetes. We arranged to leverage their supply infrastructure by providing some salary support for their Ugandan procurement officer, to ensure the ability to follow all legal requirements and permits to ship CGM supplies into Uganda.
Research concerns, Ugandan team: Ugandan team members have experience with observational research, but not RCTs.	An initial intensive research education program in Uganda was performed at study start up with ongoing education continuing throughout the study. Monitoring is done in the spirit of education. In addition to continuous remote monitoring, the UMN team visits Uganda twice per year for monitoring and, as needed, research re-education. Some of the Ugandan team have visited Minnesota and we plan to bring each of them (physicians, nurses, dietitians) to Minnesota over the grant period for more intensive training in research methods.
Research concerns, participants: Recruitment and language barriers.	Recruitment is often the biggest hurdle in clinical studies. Our pilot study demonstrated that Ugandans with T1D were eager to participate in a CGM study. Language can also be a hurdle in international studies. English is the official language of Uganda, spoken by all school students and most adults. The Ugandan staff are all bilingual in English and the local language consent forms are available in both languages, and education is delivered in both languages.
Clinical concerns, Ugandan team: Drs. [name] and [name] have pediatric diabetes training, but the nurses and dietitians on their teams have had little formal diabetes training and frequently are required to rotate to different clinical services. Because only minimal glucose data are commonly available, the Ugandan team does not have much experience with pattern recognition. CGM technology is not available in Uganda.	The budget allows salary support to train and retain three nurses, one dietitian, and two junior physicians (medical officers), who will remain with the study for its entirety, ensuring continuity. The pilot study familiarized the Ugandan team with CGM technology, and the ongoing advanced education on how to use this technology was built into the study protocol. Both initial and on-going staff education is planned, reviewing all aspects of T1D and its management, delivered in person and virtually. In addition, the Minnesota and Uganda teams together review patterns on individual participant CGM downloads monthly in a virtual format. Subspecialty training of nurses and dietitians is not common in Uganda, and thus this project is increasing local capacity for experienced pediatric diabetes care.
Clinical concerns, participants: T1D patients in Uganda are not accustomed to adjusting their own insulin doses. There is shame and stigma associated with diabetes and the fear that people with T1D will never lead “normal” lives.	The patients, who have never before been exposed to extensive glucose data, have minimal understanding of insulin action and its relation to food, activity, or hypoglycemia. An extensive patient education program is planned with didactic group education at each visit, and individual pattern recognition using their own (SMBG or CGM) data. There is also concern about the social stigma of having diabetes. CGM patches will be provided that are appropriate to their skin color so as to be less conspicuous. We are working with an NGO called the Sonia Nabeta Foundation that is empowering young adults with T1D to be peer leaders. Many of the Minnesota team members have diabetes themselves and serve as role models to show that people with diabetes can lead normal lives, including holding meaningful jobs and having a family.
Clinical concerns, Minnesota team: The younger members of the team have no experience with human (regular and NPH) insulin.	Older members of the Minnesota team and those who have previously worked in low-resource countries are experienced with these insulins and will teach the others.
If our hypothesis is correct and CGM improves diabetes metabolic control in this setting, it is meaningless unless this therapy can actually be introduced to patients there.	For the results of a positive study to impact patient care in Uganda and other sub-Saharan African countries, CGM needs to be cost effective in these low-resource settings. Thus, we involved health economists from the Ministry of Health from the beginning in project planning, and they will have an important role analyzing the data at study end.
